# Role of cerebral hypoperfusion in multiple sclerosis (ROCHIMS): study protocol for a proof-of-concept randomized controlled trial with bosentan

**DOI:** 10.1186/s13063-019-3252-4

**Published:** 2019-03-14

**Keywords:** Multiple sclerosis, Cerebral blood flow, N-acetyl aspartate, Bosentan, Axonal degeneration

## Abstract

**Background:**

Axonal degeneration is related to long-term disability in patients with multiple sclerosis (MS). The underlying mechanism remains ill understood but appears to involve axonal energetic dysfunction. A globally impaired cerebral blood flow (CBF) has been observed in the normal-appearing white matter (NAWM) of patients with MS, which is probably related to astrocytic overexpression of endothelin-1 (ET-1). Cerebral hypoperfusion has been associated with reduced mitochondrial activity and disabling symptoms (e.g. fatigue and cognitive decline) of MS. Countering this process could therefore be beneficial in the disease course. Short-term CBF restoration with a single 62.5-mg dose of the ET-1 receptor antagonist bosentan has already been demonstrated in patients with MS.

**Methods:**

The ROCHIMS study is a proof-of-concept double-blind randomized clinical trial in which patients with relapsing-remitting MS will receive either 62.5 mg bosentan or matching placebo twice daily during 28 ± 2 days. Clinical evaluation and brain magnetic resonance imaging (MRI) will be performed at baseline and treatment termination. Based on previous work, we expect a global increase of CBF in the individuals treated with bosentan. The primary outcome measure is the change of N-acetyl aspartate in centrum semiovale NAWM, which is a marker of regional axonal mitochondrial activity. Other parameters of interest include changes in fatigue, cognition, motor function, depression, and brain volume.

**Discussion:**

We hypothesize that restoring cerebral hypoperfusion in MS patients improves axonal metabolism.

Early positive effects on fatigue and cognitive dysfunction related to MS might additionally be detected. There is a medical need for drugs that can slow down the progressive axonal degeneration in MS, making this an important topic of interest.

**Trial registration:**

Clinical Trials Register, EudraCT 2017-001253-13. Registered on 15 February 2018.

**Electronic supplementary material:**

The online version of this article (10.1186/s13063-019-3252-4) contains supplementary material, which is available to authorized users.

## Background

Multiple sclerosis (MS) is a chronic neurodegenerative and inflammatory disorder of the central nerve system (CNS) mainly affecting young adults [1]. Disease pathology is characterized by two key players: intermittent bursts of focal inflammatory demyelination and widespread progressive axonal degeneration. The clinical course is highly variable. Most individuals start with a relapsing-remitting pattern, in which newly formed clinical deficits restore partially or completely over time, but after several years they often develop a secondary progressive phase of slower but continuous neurological worsening. Other patients experience primary progressive disease from onset [2].

MS relapses are triggered by the formation of focal inflammatory lesions in which auto-immune reactions against CNS myelin play a paramount role. In contrast, the steadier decline mainly results from progressive axonal loss [3]. The exact underlying mechanism of the latter remains unclear and degenerative features do not seem to correlate well with inflammatory activity, particularly in the later stages of the disease [4]. Recognition is growing that mitochondrial energy failure and oxidative stress are involved in this axonal degeneration process of MS [5, 6]. Levels of N-acetylasparate (NAA), an amino acid synthesized by mitochondria in neurons and their axons, are a marker of both axonal mitochondrial activity and axonal integrity [7] and were found to be reduced in several ^1^H-magnetic resonance spectroscopy (MRS) studies of centrum semiovale normal-appearing white matter (NAWM) in patients with MS compared to controls [8].

Perfusion-weighted magnetic resonance imaging (MRI) research conducted over the past decade has found that cerebral blood flow (CBF) is globally impaired in the NAWM of patients with relapsing-remitting MS (RRMS), primary progressive MS, and even clinically isolated syndromes suggestive for MS (CIS-MS) [9–11]. Similar observations have been made in the thalamus of CIS-MS and RRMS individuals [12]. These findings suggest that cerebral hypoperfusion is an early and integral feature of MS pathology, regardless of the clinical subtype [5]. It is unknown whether this phenomenon contributes to the progressive loss of axons, but chronically induced cerebral hypoperfusion in animal models leads to mitochondrial energy failure, oxidative stress, and eventually axonal degeneration [13]. In addition, reduced CBF has been associated with cognitive dysfunction and fatigue in patients with MS [14], which are both disabling but poorly understood disease manifestations. Reduced cerebral perfusion in small rodents resulted in neuronal loss in the hippocampal CA1 sub region, while MRI studies in MS patients revealed selective and progressive hippocampal atrophy localized initially to this CA1 sub region, which may contribute, among other factors, to cognitive impairment that occurs in many of these individuals [15, 16].

Reduced CBF in MS appears to be mediated by elevated levels of the potent vasoconstrictive agent endothelin-1 (ET-1) in the cerebral circulation, most likely derived from reactive astrocytes in focal lesions. In a previous study, the administration of a single 62.5 mg dose of bosentan, which is an ET-1 receptor antagonist, increased CBF in patients with MS up to the levels obtained in controls [5]. The main goal of the present study is to investigate in NAWM of patients with RRMS whether prolonged treatment with bosentan results in a sustained restoration of CBF and whether this enhances NAA levels, reflecting improvement of axonal mitochondrial metabolism. Our secondary aim is to explore whether CBF restoration ameliorates clinical disability (fatigue, cognition, motor function, and depression) and hippocampal volume in these patients.

## Methods and design

### Trial design

This study is a non-commercial proof-of-concept, placebo-controlled, and double-blind randomized trial, taking place at the Universitair Ziekenhuis (UZ) Brussel between October 2017 and December 2018. It is approved at national level by the Federaal Agentschap Voor Geneesmiddelen en Gezondheidsproducten (FAGG) and the local ethics committee of the UZ Brussel. The study is registered by the European Union Drug Regulating Authorities (EudraCT 2017-001253-13) as the ROCHIMS (Role Of Cerebral Hypoperfusion In Multiple Sclerosis) trial. In case of protocol modifications, all relevant stakeholders will be informed.

### Eligibility criteria

All potential participants will be screened for study inclusion according to the criteria outlined below. Each patient will be informed about the study protocol by the principle investigator and written informed consent will be obtained from all participants.

#### Inclusion criteria

Age > 18 years;Diagnosis of relapsing-remitting MS, according to the 2010 revised McDonald criteria [17];Expanded Disability Scale Score (EDSS) ≤ 4.0 [18];Use of reliable means of contraception for sexually active female patients.

#### Exclusion criteria

Clinical evidence of MS relapse within the last three months before inclusion;Pregnant or lactating women;Major liver dysfunction (AST and/or ALT > 3 times ULN);Use of cyclosporine A or glibenclamide;Allergy to bosentan.

### Randomization, study medication, and general outline

Participants will be randomly divided into a group receiving bosentan (Actelion Pharmaceuticals Ltd., Allschwil, Switzerland) 62.5 mg twice daily and another group receiving matching placebo, during 28 (± 2) days. The randomization will be performed with “research randomizer” (https://randomizer.org), using five sets of six numbers in order to achieve an equal distribution between active product and placebo. Study medication will be stored at the Hospital Pharmacy. After inclusion, patients are given a computer-generated randomization number, which is matched to a confidential treatment number by the responsible hospital pharmacist in order to assign participants to either bosentan or placebo.

Bosentan tablets are provided by Actelion Pharmaceuticals Belgium NV (Mechelen, Belgium). The production of identical-looking placebo tablets is performed by the hospital pharmacy. The tablets are taken twice daily, at 08:00 and 20:00. Adherence to the study medication will be assessed by counting the number of unused tablets returned at the second visit. All adverse events will be recorded in the “Adverse Event” section of the Case Report Form. All methods for data collection and data management will be collected in the Investigator Site File. The data monitoring committee of this trial is the Clinical Trial Centre of the University Hospital Brussel. This Clinical Trial Centre works independent from the sponsor and have no competing interests.

At baseline (day 0), patients will undergo a blood analysis, clinical assessments, transcranial Doppler (TCD), and brain MRI. All data will be pseudonymized. Only the principle investigator has the key to source data. Treatment will commence the next day (day 1). On day 28 (± 2 days), all evaluations will be repeated. All tests will be performed between 09:00 and 13:00 to avoid interference of fatigue accumulation during the day with the results. Participants are asked to refrain from alcohol or caffeine, as well as not to smoke, on the evaluation days. Two weeks after ending the trial, participants will be called to see whether any side effects has occurred in that period. After closure of the study and unblinding, only the individual patients will be informed about their study medication and all biological specimens will be destroyed. Communication of the study results will be anonymized. The trial time table is presented in Fig. 1 (Additional file 1). The study protocol is constituted taking into account the SPIRIT guidelines; the SPRIT checklist can be found as an attachment of this manuscript.

**Fig. 1 Fig1:**
[figure not shown]
ROCHIMS Trial time table. SPIRIT Figure. (See also list of abbreviations)

### Definition of outcome measures

#### Primary outcome

The primary outcome measure of the study is the change in NAA/creatine (NAA/Cr) ratios in centrum semiovale NAWM, measured with ^1^H-MRS as a part of the MRI protocol, reflecting changes in axonal mitochondrial metabolism. Based on our previous findings, we expect a rise of CBF values after treatment with bosentan [5]. The MRI protocol contains a pseudo-continuous arterial spin labeling (ASL) sequence to assess CBF in the NAWM of the centrum semiovale.

#### Secondary outcomes

Changes in fatigue, cognition, symptoms of depression, and motor function.

Clinical assessments will in each individual be performed by the same trained MS study nurse or neurologist in training to ensure consistency. They were trained in advance by an internal senior staff member to perform the neuropsychological assessments. Assessments are always scheduled in the same order: fatigue and depression scales and cognitive testing before motor function testing to avoid the interference of physical fatigue with the results. The assessments include the following:

1.1.* Fatigue scales*: Fatigue Severity Scale (FSS) [19], Modified Fatigue Impact Scale – 5-item version (MFIS-5) [20], and Fatigue Scale for Motor and Cognitive functions (FSMC) [21]. These scales assess the experienced severity of fatigue symptoms and/or the impact on cognitive, physical, and psychosocial functioning in the preceding four weeks.1.2.
*Depressive symptomatology scales*: Beck Depression Inventory (BDI-II), which is a widely used to assess the presence of symptoms of depression in the two weeks preceding the questionnaire [22].1.3.
*Cognitive performance scales*: Brief International Cognitive Assessment for Multiple Sclerosis (BICAMS): SDMT (Symbol Digit Modality Test), CVLT-II (California Verbal Learning Test), and BVMT-R (Brief Visuospatial Memory Test-Revised). The BICAMS is considered a brief and feasible tool appropriate for the cognitive assessment of MS patients [23]. The SDMT is a test of information processing speed with a high sensitivity to cognitive impairment in MS, the CVLT-II is a test for short-term and long-term verbal memory, and the BVMT-R evaluates visuospatial memory abilities [24].1.4.
*Motor function testing*: Timed 25 Foot Walk Test (T25FWT) and 9-Hole Peg Test (9HPT). T25FWT is a quantitative mobility and leg function performance test based on a timed 25-ft (or 7.62 m) walk. The patient is instructed to walk as quick as possible, without running, and safely. The time needed to perform this task, starts from the instruction to start and ends when the patient reach the 25-ft mark. Afterwards, the patient will walk the same distance back. The average of these two times is the score for the T25FWT. The 9-HPT is a quantitative measure of upper extremity (arm and hand) function. Patients have to pick up nine little pegs one by one from a container, put them as quickly as possible in nine empty holes, and once they are all in, the patients have to replace them in the container one by one. The total time for this is measured. Patients have to perform this task twice with both hands. The total score of the 9-HPT is the average time of the four trials [25].
2.Brain volumetric changes will be investigated by means of voxel-based morphometry (VBM) analysis, in which baseline T1-weighted images are subtracted from analogue follow-up images, to obtain images that represent changes of time for each individual patient. Both hippocampal regions will be selected as the main ROI for VBM analysis.3.Changes in serum levels of light chain neurofilament (NfL).

Axonal damage has been associated with a release of NfL, which is a compound of the axonal cytoskeleton, into the cerebrospinal fluid (CSF) and peripheral blood of patients with MS. New high-sensitive techniques allow the detection of NfL differences at low concentration in the serum, which has the advantage of being more easily accessible as CSF [26, 27].4.Changes in cerebral hemodynamic parameters.

Cerebral circulation will additionally be assessed by means of TCD, which is an easily applicable bedside tool, for explorative reasons.

### MRI protocol

All patients undergo a multimodal imaging protocol consisting of a high-resolution anatomical scan (T1 3D BRAVO, FOV = 256 × 256 × 180 mm^3^, resolution = 1 × 1 × 1 mm^3^, TR = 8.5 ms, TE = 3.2 ms, flip angle = 12°, TI = 450 ms; sagittal scan orientation, axial and coronal reconstructions were made afterwards), 3D fluid-attenuated inversion recovery (3D Cube T2 FLAIR, FOV = 256 × 256 × 180 mm^3^, resolution = 1 × 1 × 1 mm^3^, TR = 8000 ms, TE = 130 ms, flip angle = 90°; sagittal scan orientation, axial and coronal reconstructions were made afterwards) imaging, ASL (3D ASL, FOV = 240 × 240 mm^3^, spiral scan with 8 arms and 512 point per arm, 36 slices, slice thickness = 4.0 mm, TR = 4852 ms, TE = 10.7 ms, flip angle = 90°, TI = 2025 ms; axial plane orientation) and ^1^H-MRS (MRS PROBE, FOV = 20 × 20 mm^2^, slice thickness = 10 mm, 12 × 12 voxels, voxel thickness optimized per individual, TR = 2000 ms, TE = 144 ms, NEX = 1.6) on a 3-T machine (GE, MR 750 W Discovery).

The regions of interest for CBF and NAA/Cr + PCr quantification are the left and right centrum semiovale NAWM. FLAIR images are used to avoid inclusion of focal MS plaques. Brain volumetric changes after treatment are investigated by VBM analysis using Statistical Parametric Mapping 8 software. Total scanning time takes about 30 min.

For anatomical reference, the axial reconstructed T1-weighted BRAVO images were used; an EPISTAR (echo-planar imaging and signal targeting with alternating radio-frequency) sequence is used. The slice orientation is transversal and imaging volume is centered on the centrum semiovale. An EPI sequence with the same parameters and orientation, but without labelling pulses, is used to measure equilibrium magnetization. CBF is calculated in the NAWM of the right and left centrum semiovale by using a FLAIR scan to avoid placement in plaques. Longitudinal relaxation rates for tissue (R1app) was 0.91 s-1 and for blood (R1b) 0,59 s-1. The equilibrium magnetization of the white matter (M0WM) is used to determinate the equilibrium magnetization of blood (M0B). T2 relaxation times for white matter and blood are 55 ms and 100 ms, respectively, which brings us to the following relationship: M0B = 1.28 M0WM [10]. The final CBF results represent the average of the left and right centrum semiovale.

NAA is expressed as ratios to total creatinine (Cr, sum of Cr, and PCr), measured by ^1^H-MRS. Total Cr is supposed to maintain a relatively constant level [28]. A two-dimensional (2D) spectroscopic imaging slab, which contains multiple voxels of 1.5 cm^3^, is positioned in the centrum semiovale above the corpus callosum. Water suppressed single-slice-point-resolved spectroscopy is used with the following scan parameters: TE = 144 ms; TR = 2 s; slice thickness = 1.5 cm; in-plane resolution = 1 × 1 cm^2^; spectral band width = 2000 Hz, and 1024 sample points. NAA and Cr levels are analyzed in different voxels in the NAWM of the centrum semiovale of both cerebral hemispheres. Voxels including plaques and black holes are excluded. Analysis of the spectroscopic data is performed using GE Functool software, that allows operator-independent quantification of NAA, Cr + PCr, and NAA/Cr + PCr ratios.

### Blinding and statistical methods

Sample size calculation is based on the study of Steen et al. where NAA/Cr in centrum semiovale NAWM was 10% lower in MS patients compared to healthy controls [8]. The inclusion of 24 individuals has 90% power to detect a 10% increase in NAA/Cr in centrum semiovale NAWM in the bosentan group compared to the placebo group, with a significance level of 0.05. Taking into account asymptomatic efficiency loss (non-parametric study of 5%) and potential drop outs of 5%, inclusion of 30 patients should be sufficient.

All study participants and investigators will remain blinded throughout the complete treatment and evaluation period. Unblinding will only be done after final database lock or in case of emergencies and serious adverse events.

All statistics will be performed by an independent biometrician and with SPSS software, version 25. The Wilcoxon signed-rank test for paired samples will be used to compare differences within the two treatment groups; the Mann–Whitney U test will be used to compare differences between the groups. Fisher’s exact test will be used to compare categorical variables. Spearman’s correlation coefficient will be used to correlate continuous data. The level for statistical significance is defined as *p* < 0.05.

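### The primary between-arm comparison is a Mann–Whitney test on change that subtracts baseline NAA/Cr but does not adjust for it; a baseline-adjusted analysis would be more precise at almost no cost

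*Protocol article*

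**What the plan says.** Three places in the Protocol article together define the primary comparison.

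- **Outcome** (Primary outcome): "The primary outcome measure of the study is the change in NAA/creatine (NAA/Cr) ratios in centrum semiovale NAWM".
- **Timing** (Randomization, study medication, and general outline): "At baseline (day 0), patients will undergo a blood analysis, clinical assessments, transcranial Doppler (TCD), and brain MRI". On day 28 (± 2 days), "all evaluations will be repeated". Each patient who completes therefore has a baseline and a follow-up NAA/Cr.
- **Tests** (Blinding and statistical methods): between arms, "the Mann–Whitney U test will be used to compare differences between the groups"; within arms, "The Wilcoxon signed-rank test for paired samples will be used to compare differences within the two treatment groups".

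The sample size paragraph confirms that a rank test is intended, since it adds 5% for non-parametric efficiency loss. The article names no covariate and no model for any comparison.

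**The concern.** A change score is follow-up minus baseline, so it fixes the weight on baseline at 1. When baseline and follow-up are imperfectly correlated, the best weight is smaller (rho itself when the two variances are equal), and the fixed weight carries surplus baseline noise into the comparison. ANCOVA estimates the weight from the data.

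In a trial of 30 patients, this noise matters most if the true effect is smaller than planned. That is a realistic possibility: the planned 10% increase equals the whole MS-versus-control deficit cited as the basis of the sample size, so the plan assumes full normalisation within about four weeks.

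The same point can be put in terms of chance imbalance. The article describes no stratification on baseline NAA/Cr. With 14 evaluable patients per arm, the difference in baseline means has standard error √(2/14) = 0.38 SD. It therefore exceeds 0.3 SD in about 43% of trials and 0.5 SD in about 19%. A given imbalance shifts the expected change-score contrast by (1−rho) times its size, for example 0.25 SD when the imbalance is 0.5 SD and rho is 0.5. This is not an additional loss; it is the surplus variance seen from within one trial.

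**Working it through.** **Inputs from the article.** 24 evaluable patients (12 per arm), 90% power, a 10% increase, significance level 0.05 (sidedness not stated; two-sided assumed), 5% for the rank test, 5% for drop-out, 30 enrolled. **Not in the article:** the SD of NAA/Cr, the SD of its change, and rho.

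**Step 1. The plan's own figure.** "The inclusion of 24 individuals has 90% power to detect a 10% increase in NAA/Cr" cannot be reproduced without an SD, so I solved for the SD that makes it true.

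- Normal approximation: SD = 10 × √(12/2) / (1.960 + 1.282) = 24.49 / 3.242 = 7.6% of the mean.
- Noncentral t: SD = 7.2%, a standardised effect of 10 / 7.2 = 1.39.
- One-sided, the values would be 8.4% and 8.1%.
- Inflation: 24 / 0.95 / 0.95 = 26.6. Rounded up to whole sets of six, as used for the allocation, this gives 30.

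**Step 2. Variance.** Let both visits have variance σ² and correlation rho.

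- Change score: 2σ²(1 − rho) per patient.
- ANCOVA residual: σ²(1 − rho²) per patient.
- Ratio: (1 − rho²) / [2(1 − rho)] = (1 + rho)/2, a reduction of (1 − rho)/2.

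| Assumed rho | Variance ratio | Variance saved | SE saved | ANCOVA patients equivalent to 30 on change |
|---|---|---|---|---|
| 0.3 | 0.65 | 35% | 19% | 19.5 |
| 0.5 | 0.75 | 25% | 13% | 22.5 |
| 0.7 | 0.85 | 15% | 8% | 25.5 |
| 0.8 | 0.90 | 10% | 5% | 27 |
| 0.9 | 0.95 | 5% | 2.5% | 28.5 |

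The last column is 30 × (1 + rho)/2, before the loss of one degree of freedom.

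**Step 3. Power.** Simulation with 15 per arm, normal data, equal variances, two-sided 0.05 and 20,000 runs per setting. The 7.2% from Step 1 is read as the SD of change, the quantity the plan analyses.

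| Effect | Mann–Whitney on change | ANCOVA, rho 0.3 | rho 0.5 | rho 0.7 | rho 0.9 |
|---|---|---|---|---|---|
| 10% (planned) | about 94% | 99% | 99% | 97% | 96% |
| 5% (half) | 41–43% | 61% | 55% | 50% | 46% |

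A repeat run with the same settings agreed to within about one percentage point. With no true effect, the Mann–Whitney test rejected in 4.3–4.6% of runs, so it holds its level.

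**Step 4. Where the gain comes from.** A t-test on change, without adjustment, has about 95–96% power at the planned effect and 45% at half. At rho 0.9, nearly all of the difference between Mann–Whitney and ANCOVA thus reflects a parametric test on normal data. At rho 0.3 to 0.5, most of it comes from the adjustment.

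**Step 5. A rank-based adjustment.** With 14 per arm and the planned effect scaled to the SD of change, Quade's rank ANCOVA against Mann–Whitney on change gave 98% v 93% (rho 0.3), 96% v 92% (0.5), 94% v 93% (0.7), 92% v 93% (0.8) and 87% v 94% (0.9). It gains at low rho and loses at high rho.

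**The case against.** The strongest reply is that the plan chose between two valid tests and budgeted for its choice. The Mann–Whitney test keeps its level and, if the implied SD is the SD of change, exceeds the 90% target with 30 patients. The gain depends on a rho that the article does not give. The spectroscopy section of the MRI protocol describes analysis of several voxels in both hemispheres; such averaging tends to raise rho and shrink the gain. ANCOVA also gives up the distribution-free property that the sponsor evidently wanted. All of this stands, and it limits the point to an efficiency gain of uncertain size.

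A reader might infer more than the article supports:

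- *That baseline is ignored.* It is subtracted. It would be ignored only if the between-group comparison used day-28 values alone. The test sentence is loose, but the outcome definition points to change.
- *That the result would be biased or the test invalid.* Neither follows. Chance imbalance averages out over randomisations, and the simulated type I error is at or below 5%.
- *That the change is the difference of two single readings.* The multi-voxel, two-hemisphere description says otherwise.
- *That power falls well short.* Simulated figures such as 81% against 95% (14 per arm) arise only when the implied SD is read as a cross-sectional SD and rho is as low as 0.3. The article supports neither assumption.
- *That no effect estimate is planned.* A condensed article may leave estimates and intervals to the full protocol or SAP, and a Hodges–Lehmann shift can accompany the Mann–Whitney test.

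**Conclusion.** The point holds as an inexpensive improvement to a stated method. The primary comparison uses baseline NAA/Cr only by subtraction, and adjusting for it would save (1 − rho)/2 of the variance. The saving is worthwhile at low or moderate rho and slight at 0.9. The power gain is modest at the planned 10% effect and more useful at half of it, where power is below 50% without adjustment.

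The variance figures assume equal variances at the two visits and an assumed rho. The power figures further assume normal data, 15 evaluable patients per arm, two-sided testing and 7.2% as the SD of change. With unequal visit variances the percentages would change, but in large samples ANCOVA would still be no less precise than the change score, because it estimates the coefficient. The absence of an SD behind the 24 patients is a separate matter.

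**What to change.** Before unblinding, replace the between-arm sentence for the primary outcome with wording such as: *Day-28 NAA/Cr will be compared between arms by analysis of covariance on the untransformed values, with baseline NAA/Cr as covariate; the adjusted mean difference and its 95% confidence interval will be reported. A Mann–Whitney test on the change in NAA/Cr will be the non-parametric sensitivity analysis.*

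- Use the same adjustment for the scalar secondary outcomes: CBF, the clinical scales and tests, and serum NfL. It does not transfer directly to hippocampal volume, which is analysed by voxel-based morphometry on subtracted images.
- Do not offer Quade's rank ANCOVA as an equivalent alternative, since it can lose power to the planned test at high rho.

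**Cost.** A sentence or two in the analysis section, one degree of freedom, and reliance on approximately normal residuals, which the sensitivity analysis covers. No extra patients or measurements are needed, SPSS 25 provides the model, and the article reports that recruitment was still open.
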